**EMS mission data**		
Priority out (Emergency dispatch centre, EMD)	Priority 1-3, where 1 is highest, i.e. lights and sirens	EMS medical record
Priority in (Emergency medical services, EMS)	Priority 1-4, where 1 is highest, i.e. lights and sirens	EMS medical record
EMS missions created at EDM, time stamp		EMS medical record
EMS mission received from EMD, time stamp		EMS medical record
EMS mission acknowledged by EMS, time stamp		EMS medical record
EMS arrival on scene, time stamp		EMS medical record
EMS patient transport initiated, time stamp		EMS medical record
EMS arrival at destination, time stamp		EMS medical record
EMS return initiated, time stamp		EMS medical record
Destination for EMS transport	Type of care facility to which the patients were transported	EMS medical record
Triage colour according to EMS triage	Red, Orange, Yellow or Green	EMS medical record
Triage colour according initial vital signs	Red, Orange, Yellow or Green	EMS medical record
Triage colour according to patient signs and symptoms	Red, Orange, Yellow or Green	EMS medical record
**Demographics and medical history**		
Age	Years	Hospital medical record
Sex	Male/Female	Hospital medical record
Acute coronary syndrome (ACS)	Any of the following ICD-10 codes: I200, I21, I22, I24, I252 or I254	Hospital medical record
Chronic obstructive pulmonary disease (COPD)	Any of the following ICD-10 codes: J44	Hospital medical record
Angina pectoris	Any of the following ICD-10 codes: I201, I208 or I209	Hospital medical record
Hypertension	Any of the following ICD-10 codes: I10, I11, I12, I13 or I15	Hospital medical record
Diabetes mellitus	Any of the following ICD-10 codes: E10, E11 or E14	Hospital medical record
Heart failure	Any of the following ICD-10 codes: I110, I130, I132, I255, I311, I420, I421, I422, I424, I425, I426, I427, I429 or I50	Hospital medical record
Stroke (ischaemic)	Any of the following ICD-10 codes: I63, I64, I65 or I66	Hospital medical record
Renal disease	Any of the following ICD-10 codes: I12, I13, I701, N17, N18, N19, N280, N288 or N289	Hospital medical record
Rheumatism	Any of the following ICD-10 codes: M05 or M06	Hospital medical record
Cancer	Any of the following ICD-10 codes: C1-9	Hospital medical record
Atrial fibrillation/flutter	Any of the following ICD-10 codes: I48	Hospital medical record
Psychiatric diagnosis	Any of the following ICD-10 codes: F1-6	Hospital medical record
Hyperlipidemia	Any of the following ICD-10 codes: E78	Hospital medical record
Previous coronary artery bypass graft (CABG) operation	Any of the following ICD-10 or procedure codes: FNA, FNC, FNE or Z951	Hospital medical record
Previous percutaneous coronary intervention (PCI)	Any of the following ICD-10 or procedure codes: FNG or Z955	Hospital medical record
Smoking	Never smoked; Stopped smoking >1 months ago; Still smoking one month before EMS mission; Unknown	EMS study protocol
**Vital sign (first registered value during EMS mission)**		
Breathing rate		EMS record
Oxygen saturation		EMS record
Systolic blood pressure		EMS record
Diastolic blood pressure		EMS record
Heart rate		EMS record
Level of consciousness		EMS record
Body temperature		EMS record
B-glucose		EMS record
**Clinical presentation**		
Paleness	Based on EMS assessment	EMS study protocol
Clamminess	Based on EMS assessment	EMS study protocol
Nausea (and/or vomiting)	According to patient or witnesses	EMS study protocol
Pain onset initiating EMS contact > 3 h ago	According to patient or witnesses	EMS study protocol
Continuous pain ≥20 min	According to patient or witnesses	EMS study protocol
Pain onset in connection with physical activity	According to patient or witnesses	EMS study protocol
Sudden pain debut (seconds)	According to patient or witnesses	EMS study protocol
Palpation tenderness	According to patient	EMS study protocol
Pain affected by movement	According to patient	EMS study protocol
Pain affected by breathing	According to patient	EMS study protocol
Affected breathing	According to patient	EMS study protocol
*Pain quality*		
Pressuring/heaviness	According to patient	EMS study protocol
Stabbing	According to patient	EMS study protocol
Discomfort	According to patient	EMS study protocol
*Pain localisation*		
Central pain	According to patient	EMS study protocol
Left side of chest	According to patient	EMS study protocol
Right side of chest	According to patient	EMS study protocol
Lower part of chest	According to patient	EMS study protocol
*Size of area affected by pain*		
Two inch diameter	According to patient	EMS study protocol
Size of patient’s palm	According to patient	EMS study protocol
Entire chest	According to patient	EMS study protocol
*Pain radiation*		
Jaw/throat	According to patient	EMS study protocol
Left arm	According to patient	EMS study protocol
Right arm	According to patient	EMS study protocol
Back	According to patient	EMS study protocol
Stomach	According to patient	EMS study protocol
No other pain	According to patient	EMS study protocol
Pain intensity according to NRS/VAS	According to patient	EMS study protocol
*Verbal pain intensity scoring*	According to patient	
No pain		EMS study protocol
Mild pain		EMS study protocol
Moderate pain		EMS study protocol
Severe pain		EMS study protocol
**Electrocardiogram**,** ECG**		
*EMS ECG interpretation*		
Sinus Rhythm, SR	EMS assessment	EMS study protocol
Atrial Fibrillation/Flutter, AF	EMS assessment	EMS study protocol
ST-Elevation	EMS assessment	EMS study protocol
ST-Depression	EMS assessment	EMS study protocol
T-wave Inversion	EMS assessment	EMS study protocol
Normal ECG	EMS assessment	EMS study protocol
*ECG interpretation by expert in retrospect*		
Sinus Rhythm, SR	ECG expert assessment	Hospital medical record
Sinus Bradycardia	ECG expert assessment	Hospital medical record
Sinus Tachycardia	ECG expert assessment	Hospital medical record
Supraventricular Tachycardia, SVT	ECG expert assessment	Hospital medical record
Atrial Fibrillation/Flutter, AF	ECG expert assessment	Hospital medical record
Ventricular Tachycardia, VT	ECG expert assessment	Hospital medical record
Atrial Pacing	ECG expert assessment	Hospital medical record
Ventricular Pacing	ECG expert assessment	Hospital medical record
AV-block II type 1	ECG expert assessment	Hospital medical record
AV-block II type 2	ECG expert assessment	Hospital medical record
AV-Block III	ECG expert assessment	Hospital medical record
ST-Elevation	ECG expert assessment	Hospital medical record
ST-Depression	ECG expert assessment	Hospital medical record
T-wave Inversion	ECG expert assessment	Hospital medical record
Q-wave	ECG expert assessment	Hospital medical record
Premature Ventricular Contraction, PVC	ECG expert assessment	Hospital medical record
Premature Atrial Contractions, PAC	ECG expert assessment	Hospital medical record
Left Bundle Branch Block, LBBB	ECG expert assessment	Hospital medical record
Right Bundle Branch Block, RBBB	ECG expert assessment	Hospital medical record
Sinus rhythm and none of abnormalities above	ECG expert assessment	Hospital medical record
QRS-duration	ECG expert assessment	Hospital medical record
Prehospital Troponin I value	Analysed using Siemens Atellica VTLi	EMS study protocol
Time stamp for Troponin I value		EMS study protocol
Troponin T value	Analysed inhospital using Roche Cobas, modul e801, blood sample retrived during EMS missions	Hospital medical record
Time stamp for blood sample collection for Troponin T		Hospital medical record
ED visit within 72 h from EMS mission		Hospital medical record
Hospital admission to hospital ward		Hospital medical record
Diagnosis on hospital discharge, ED	ICD-10 code	Hospital medical record
Diagnosis on hospital discharge, Epicris	ICD-10 code	Hospital medical record
30-day mortality from EMS mission		Hospital medical record

### Outcome measures

#### Primary outcome

Proportion of patients classified as low-risk by the decision support tool.The proportion of patients, among those classified by the decision support tool as low-risk, who at follow-up turn out to have a high-risk condition.

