Improved prehospital assessment and risk stratification, thus accurately and safely identifying patients suitable for non-conveyance, could prevent unnecessary transport to the ED. It would thus reduce ED crowding and overburdening sparse EMS resources [20]. It would probably also reduce healthcare costs [21, 22]. Furthermore, it would allow patients to avoid unnecessary EMS transport and long waiting times in the ED.

In the BRIAN 1 (BRöstsmärta In AmbulaNs (Swedish), EMS Chest Pain (English)) research programme [6, 17], we previously studied potential improvements in the EMS’ risk stratification of patients with chest pain. We have now started the data collection for BRIAN 2, in which we aim to develop an EMS decision support tool for the risk assessment of chest pain patients using AI and high-sensitivity troponin I. In BRIAN 2, we also aim to validate a previously developed decision support tool from BRIAN 1 [17] and the application of the European Society of Cardiology ESC 0/1 algorithm in the EMS setting [23]. This paper aims to present the study protocol and the initial feasibility of the study.

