### Population

Adult, unselected, EMS patients with a chief complaint of chest pain as assessed by EMS personnel.

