### Definitions

Risk condition classification is based on the diagnosis given at discharge from the hospital according to the physician in charge. A low-risk condition is defined as a diagnosis with no medical need for hospital treatment, suitable for non-conveyance. This also includes patients with chest pain who remain on scene, who do not visit the ED within 72 h and who do not die within 7 days.

A high-risk condition is defined as a time-sensitive condition with relatively high mortality rate in need of immediate medical care when seen retrospectively, for which transport to the hospital with highest priority is called upon. These definitions are the same as those used in BRIAN 1 [6].

An intermediate-risk condition is defined as a diagnosis probably in need of hospital care but for which time is not judged to be a critical factor. That is, it does not fulfil either of the definitions above.

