### Interim safety analysis

An interim analysis was conducted after the inclusion of the first 100 patients to ensure patient safety during the initial phase of the study. The primary objective of this interim analysis was to verify that no patients were non-conveyed based solely on troponin readings. This analysis served as an a priori safety check to confirm that EMS decisions regarding patient transport were based on a comprehensive clinical assessment rather than troponin results alone. Upon arrival at the scene, the EMS followed a standardised clinical guideline that includes a thorough evaluation of the patient’s clinical presentation, medical history, vital signs and ECG findings.

During the interim analysis, detailed data from 141 patients was reviewed to assess the EMS’ decision-making process. Each case was evaluated to determine the rationale behind the conveyance decision. Specifically, the analysis focused on identifying instances in which the troponin reading could have disproportionately influenced the decision not to transport a patient. Patient outcomes were tracked to identify any adverse events according to the definition or need for subsequent medical attention after a non-conveyance decision. This step ensured that patients who were not transported did not experience adverse outcomes that could have been prevented or mitigated by hospital transport.

Among the 141 patients, a total of 21 patients (14.9%) were not conveyed after assessment by the EMS. The rate of non-conveyance is thus similar to, and even lower than, that of the patient population with chest pain assessed within the EMS organisations (approximately 20% non-conveyance rate). In accordance with the study outcome, we encourage EMS personnel to obtain a full history of the patient care event, including physician diagnosis at hospital discharge, which may explain the increased conveyance rate. Moreover, since the troponin analysis results are not being blinded, elevated troponin levels could result in transporting patients to the ED also in the case of patients who would normally be non-conveyed.

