Of the patients who were non-conveyed and referred to lower levels of care, seven patients (33%) sought emergency care and were admitted to the ED within 72 h. An evaluation of patient outcomes revealed that none of the non-conveyed patients fell into the high-risk category. All but one were classified as low-risk. This single patient in the intermediate-risk category was classified based on the final diagnosis, in accordance with the study definitions previously described by Wibring et al. [6].

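### Both primary outcomes pool patients already left on scene with those transported, and neither is specified by conveyance status, although the avoidable-transport and safety conclusions concern transported patients

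*Protocol article*

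**What the plan says.** The Population section of the protocol article describes the cohort as "Adult, unselected, EMS patients with a chief complaint of chest pain as assessed by EMS personnel". Outcome measures sets two primary outcomes on that cohort: the "Proportion of patients classified as low-risk by the decision support tool", and the proportion "among those classified by the decision support tool as low-risk, who at follow-up turn out to have a high-risk condition". Conveyance enters neither.

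The Introduction gives the purpose: "accurately and safely identifying patients suitable for non-conveyance, could prevent unnecessary transport to the ED".

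Definitions bases risk class on the discharge diagnosis, with one addition to the low-risk class: "This also includes patients with chest pain who remain on scene", provided there is no ED visit within 72 h and no death within 7 days.

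The Interim safety analysis reports: "Among the 141 patients, a total of 21 patients (14.9%) were not conveyed after assessment by the EMS". It puts the rate among chest pain patients in these EMS organisations at roughly 20%. Seven of the 21 reached the ED within 72 h, "none of the non-conveyed patients fell into the high-risk category", and all but one were classed as low-risk.

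Three items are limited to transported patients. Two are secondary outcomes in patients flagged low-risk and taken to an ED: admission to a ward, and the distribution of final diagnoses. The third is the subgroup analysis of the added utility of troponin.

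**The concern.** A transport can be prevented only in a patient who would otherwise be transported. Patients whom crews already leave on scene raise the low-risk yield, but flagging them saves no transport.

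They also enter the denominator of the miss rate. Those with no early ED visit or death are low-risk by rule, so none of them can enter its numerator, whatever condition they had.

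Both effects favour the tool. At stake is how the two headline figures are read. A reader will take the yield as the scope for additional non-conveyance, and the miss rate as the risk of leaving at home a patient who is now transported. The pooled outcomes answer neither question directly.

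**Working it through.** **The plan's own figures.** 21/141 = 14.9% and 7/21 = 33%, both as stated. Patients without an ED visit in 72 h: 21 − 7 = 14, which is 14/21 = 67% of the non-conveyed and 14/141 = 9.9% of those reviewed. These 14 are low-risk by rule unless they died within 7 days. The planned sample size of 1,857 also reproduces from its stated inputs. It concerns model development and is not affected by this point.

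**Inputs**
- N = 2,000 (Sample size).
- f, the share not conveyed: 21/141 = 0.149 (interim) or 0.20 (usual practice).
- L, the share of all patients the tool flags low-risk: not in the documents. Assumed 0.50 or 0.68. The upper value borrows the 68% event rate under Sample size, read as the low-risk share.
- s, the share of non-conveyed patients the tool flags: not in the documents. The low assumption is s = L (flagged no more often than others). The high assumption is s = 20/21 = 0.952, borrowed from the interim low-risk classification.

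**Formulas**
- Share of the flagged group already at home: h = f·s/L.
- Flagged patients who were transported, the ceiling on avoidable transports: N(L − f·s).
- Conveyed-only miss rate divided by pooled miss rate: (1 − m)/(1 − h), where m is the share of misses found in non-conveyed patients. With m = 0 this is 1/(1 − h).

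**Results with m = 0**

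| f | L | s | h | Transported and flagged, against all flagged | Miss-rate ratio |
|---|---|---|---|---|---|
| 0.149 | 0.68 | 0.68 | 0.149 | 1,157 against 1,360 | 1.18 |
| 0.20 | 0.68 | 0.68 | 0.200 | 1,088 against 1,360 | 1.25 |
| 0.149 | 0.50 | 0.50 | 0.149 | 851 against 1,000 | 1.18 |
| 0.20 | 0.50 | 0.50 | 0.200 | 800 against 1,000 | 1.25 |
| 0.149 | 0.68 | 0.952 | 0.209 | 1,076 against 1,360 | 1.26 |
| 0.20 | 0.68 | 0.952 | 0.280 | 979 against 1,360 | 1.39 |
| 0.149 | 0.50 | 0.952 | 0.284 | 716 against 1,000 | 1.40 |
| 0.20 | 0.50 | 0.952 | 0.381 | 619 against 1,000 | 1.62 |

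Example, last row: f·s = 0.20 × 0.952 = 0.190; h = 0.190/0.50 = 0.381; 2,000 × (0.50 − 0.190) = 619; 1/(1 − 0.381) = 1.62. A pooled miss rate of 1.0% would then be 1.62% among transported patients.

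**Direction.** The ratio exceeds 1 whenever m < h, that is, whenever non-conveyed patients hold a smaller share of the misses than of the flagged group. The interim count of high-risk conditions among them is 0/21. That is a small sample (exact two-sided 95% upper limit 1 − 0.025^(1/21) = 16%), but the low-risk rule pushes the same way for every patient without an early ED visit or death. Hence the direction is probable rather than certain. That the yield exceeds the avoidable transports is certain as soon as any non-conveyed patient is flagged.

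**The case against.** The strongest reply is that the all-patient denominator is the right one for the question asked. The tool would be used on scene, before any conveyance decision, in unselected chest pain patients, and the first scientific question asks how many it would class as low-risk and suitable to stay. The Introduction adds that little is known about the patients now left at home. This stands, and the all-patient outcomes should stay. A reader might infer that the primary outcomes are simply wrong, or that the protocol credits the tool with transports it does not prevent. The documents do not support that: nowhere is the first outcome called transports prevented.

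A second reply is that the secondary outcomes already cover low-risk transported patients, including their final diagnoses. This stands in part. The diagnoses could reveal most of the misses in that group, but no yield or miss rate in conveyed patients is defined from them.

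A third is that conveyance within the study is contaminated. Crews see the troponin result, and the article itself says that high values may prompt transport and fears that low values may prompt non-conveyance. Troponin is also an input to the tool. A reader might infer that conveyed patients should replace all patients as the headline group. This contamination is why that goes too far: those conveyed in the study are not exactly those conveyed in usual practice.

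A fourth is that the shift is small beside sampling error. As an illustration, suppose 70% of 1,360 low-risk patients are flagged (952) and 10 high-risk patients are missed, all of them conveyed. The pooled rate is 10/962 = 1.04%, with a 95% interval of about 0.5% to 1.9%. Removing 0.149 × 2,000 × 20/21 × 0.70 = 199 flagged patients who were not conveyed gives 10/763 = 1.31%, inside that interval. That is true, but the shift is systematic, runs in one direction, and is not reflected in the interval.

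Finally, stratified reporting is often left to an analysis plan. The article does, however, fix the two primary outcomes and their denominators, and these are what will be quoted.

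**Conclusion.** The point holds in a limited form. The pooled outcomes are legitimate descriptions of the tool in the population it is meant for. They do not measure avoidable transport, and they probably understate the miss rate among transported patients.

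With no misses among the non-conveyed, the conveyed-only miss rate is about 1.2 times the pooled rate if these patients are flagged no more often than others. It is 1.26 to 1.62 times if 20/21 of them, and 50% to 68% of all patients, are flagged. Over the same scenarios, 15% to 38% of the tool's low-risk group would already be at home.

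The sizes rest on assumed flag rates and on 0/21 interim cases, and the upper end uses the usual-practice rate of 20% rather than the 14.9% seen among participants reviewed. They are ranges for planning, not estimates of bias. Missing diagnoses in patients left on scene are a separate verification problem, but they bear on this point because they make misses in that group largely unobservable.

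**What to change.** - Keep both all-patient primary outcomes.
- Prespecify both by conveyance status as well, using the transport destination and time stamps already listed in Table 1.
- Base any statement about avoidable transport, or about the risk of leaving at home a patient who is now transported, on the conveyed stratum.
- Report how many patients in the low-risk denominator received that label without a hospital diagnosis.
- State as a limitation that conveyance in the study may have been influenced by the unblinded troponin result.

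The cost is a wording change and one stratified analysis on data already being collected. The conveyed stratum has 15% to 20% fewer patients, so its intervals are somewhat wider, and its figures will probably look less favourable. The choice should be fixed before the tool's results are known.

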Chest pain is one of the most common reasons for contacting the EMS [3–5]. However, the above-described methods for differentiating EMS care are generally not available for patients with chest pain. Approximately 15% of EMS chest pain patients have a high-risk condition, for example acute myocardial infarction (AMI), pulmonary embolism or aortic dissection [6, 7]. Of these, fewer than a one-third have an ST-elevation myocardial infarction (STEMI) [6, 8], entitling them to fast-track transportation directly to percutaneous coronary intervention (PCI) centres for immediate revascularisation [9]. The remaining patients with a high-risk condition, suffering mainly from non-ST elevation myocardial infarction (NSTEMI), are transported to often crowded EDs [6]. In the ED, these patients receive further care and investigation along with the 2/3 of all EMS chest pain patients, which often in retrospect, are without need of hospital care, given their diagnosis at hospital discharge [6]. EMS differentiation between patients with time-sensitive conditions and patients without hospital care needs is thus largely deficient. It is difficult for EMS personnel to identify which patients are suffering from a high-risk condition requiring prompt hospital care and which patients are suitable for non-conveyance or referral to primary care. This is the reason why a vast majority of patients with chest pain are transported to the ED for further investigation even if hospital care is not necessary [10]. Furthermore, little is known about chest pain patients which today does not convey [6, 7, 11] and the accuracy of the EMS assessment [11].

In recent years, interest in prehospital analyses of troponins to improve prehospital patient assessment and risk stratification has increased [12–16]. However, these studies used 4th generation troponin analyses, and little is known about the prehospital use of 5th generation, i.e., high-sensitivity troponin analyses. Furthermore, previous studies have focused on the prehospital use of the HEART score even though the HEART score was developed on hospital data for hospital use and does not take high-risk diagnoses other than AMI into account [17]. In addition to prehospital analyses of troponins, the use of artificial intelligence (AI) algorithms [10, 18] and other statistical models has shown promising results regarding the identification of chest pain patients suitable for non-conveyance [17, 19].

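### Neither primary outcome registers an intermediate-risk patient whom the tool calls low-risk, although the protocol's own definitions make that a misclassification

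*Protocol article*

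**What the plan says.** Under Primary outcome, the protocol article lists two measures. The first is "Proportion of patients classified as low-risk by the decision support tool". The second is the proportion, "among those classified by the decision support tool as low-risk, who at follow-up turn out to have a high-risk condition".

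The Definitions section sorts patients into three classes by discharge diagnosis:

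- Low: "A low-risk condition is defined as a diagnosis with no medical need for hospital treatment, suitable for non-conveyance". Some patients who stay on scene also count as low-risk, subject to conditions on later ED visits and death.
- High: a time-sensitive condition with relatively high mortality.
- Intermediate: "An intermediate-risk condition is defined as a diagnosis probably in need of hospital care", where time is not judged critical. The section adds: "That is, it does not fulfil either of the definitions above".

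The first scientific question asks how many patients the tool will class as low-risk and suitable for non-conveyance.

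The Secondary outcome section adds ward admission among tool-low-risk patients taken to an ED, the final diagnoses in that group, the two primary measures by sex and age, and the tool's predictive ability for low-risk and high-risk patients.

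**The concern.** The protocol ties suitability for non-conveyance to having no medical need for hospital treatment. The primary error rate counts something narrower: a time-critical condition. Intermediate-risk patients fall between the two. If the tool calls one of them low-risk, the protocol's definitions make that a wrong call. The first primary outcome nevertheless counts it as yield, and the second places it only in the denominator.

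What is at stake is how the headline pair can be read. A large low-risk group with a small high-risk proportion could be taken as evidence that the group can safely stay at home, while an appreciable part of it probably needed hospital care. The two primary figures alone would not show this.

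**Working it through.** **Inputs**

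- Planned sample: 2,000 (Sample size).
- High-risk share: "Approximately 15% of EMS chest pain patients have a high-risk condition" (Introduction).
- Low-risk share: 68%, the event rate in Sample size. That section does not name the event. The Introduction gives a similar figure: "2/3 of all EMS chest pain patients, which often in retrospect, are without need of hospital care".
- Intermediate share: not stated. Assumed as the remainder, 100 − 68 − 15 = 17%. With two-thirds in place of 68% it is 100 − 66.7 − 15 = 18.3%.
- Tool performance: not known yet, so assumed, with alternatives shown.

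**Which event does the 68% describe?** The stated 1857 can be reproduced. An AUC of 0.85 at 68% prevalence gives, by simulation, a Cox-Snell R² of 0.314 to 0.316. The shrinkage criterion is n = P / ((S − 1) ln(1 − R²/S)) with P = 80 and S = 0.9.

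- It gives 1848 to 1866 over three simulations; R² = 0.315 gives 1857.
- The R² criterion gives about 1817 to 1820, and the average-risk criterion 1.96² × 0.68 × 0.32 / 0.05² rounds up to 335, so shrinkage decides.
- A 15% event, which would be high-risk against the rest, needs about 3,000 to 3,030 and does not match.

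The sample size is thus consistent with a model of low-risk against all others, though the text does not say so.

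**Algebra.** Let l, m and h be the truly low-, intermediate- and high-risk patients the tool calls low-risk, out of N.

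- Outcome 1 = (l + m + h) / N
- Outcome 2 = h / (l + m + h)

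With l and h fixed, raising m always raises outcome 1. It lowers outcome 2 if h > 0 and leaves it at 0 if h = 0. This direction needs no assumption about the shares.

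**Illustration.** Classes: 1,360 low, 340 intermediate, 300 high. Assume l = 1,000 and h = 8.

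| | m = 0 | m = 340 |
|---|---|---|
| Outcome 1 | 1,008 / 2,000 = 50.4% | 1,348 / 2,000 = 67.4% |
| Outcome 2 | 8 / 1,008 = 0.79% | 8 / 1,348 = 0.59% |
| Intermediate-risk share of the low-risk group | 0% | 340 / 1,348 = 25.2% |
| High- or intermediate-risk share | 8 / 1,008 = 0.79% | 348 / 1,348 = 25.8% |

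**Other assumed performance.** Let the tool call 60% of low-risk (816) and 3% of high-risk patients (9) low-risk.

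| Intermediate called low-risk | Outcome 1 | Outcome 2 | High or intermediate |
|---|---|---|---|
| 0% | 825 / 2,000 = 41.25% | 9 / 825 = 1.09% | 1.09% |
| 25% (85) | 910 / 2,000 = 45.50% | 9 / 910 = 0.99% | 94 / 910 = 10.3% |
| 50% (170) | 995 / 2,000 = 49.75% | 9 / 995 = 0.90% | 179 / 995 = 18.0% |
| 100% (340) | 1,165 / 2,000 = 58.25% | 9 / 1,165 = 0.77% | 349 / 1,165 = 30.0% |

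Going from none to all of the intermediate patients, outcome 2 falls from 0.37% to 0.26% with 60% and 1%, and from 1.36% to 1.04% with 80% and 5%.

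**How fragile is the fall in outcome 2?** In the first illustration, outcome 2 stays at 8/1,008 when h / (1,340 + h) = 8 / 1,008, that is h = 10.72. Three extra missed high-risk patients reverse the fall: 11 / 1,351 = 0.81%. If the other 360 low-risk patients also come in, six extra suffice: 14 / 1,714 = 0.82%.

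**The case against.** A yield paired with a rate of missed time-critical disease is a coherent choice, and the protocol says time is not critical in intermediate conditions. That stands: the pair is incomplete for the question of suitability, but not incoherent.

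A reader might infer that the primary outcomes will pull the choice of model or cut-off towards a tool that overlooks intermediate-risk patients. The article does not support this. Statistical analyses tunes the LASSO and machine-learning models by cross-validated deviance and evaluates performance by pseudo-R², AUC and calibration. No cut-off rule is tied to the primary outcomes. If the model is fitted to low-risk against the rest, as the 68% suggests, fitting itself would penalise this error.

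A reader might also infer that both outcomes always look better. They need not. A looser cut-off would be expected to bring in some high-risk patients too, and a few are enough to reverse outcome 2.

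Nor does the tool send anyone home in this study. It is observational, and care follows organisational guidelines. The point concerns classification and reporting only.

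Finally, the secondary outcomes do reveal part of the error. Final diagnoses would show intermediate conditions, and predictive ability for low-risk could be read as low against the rest. But ward admission covers only transported and admitted patients, the diagnoses are tied to that group, and the predictive-ability item names low- and high-risk only. Patients left on scene who later seek care are not clearly covered. The interim safety analysis shows that such patients exist: 7 of 21 non-conveyed patients came to an ED within 72 h. One of the 21 was classed as intermediate-risk and was reported separately, so the team already distinguishes the classes in practice.

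**Conclusion.** The point holds in a limited form. Calling an intermediate-risk patient low-risk is an error under the protocol's definitions, and neither primary outcome registers it. That follows from the definitions alone.

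The size is illustrative. It rests on an inferred 17% intermediate share, an unnamed 68% event taken as low-risk, assumed tool performance, and missed high-risk patients held fixed. Under the assumptions tried, with all intermediate patients called low-risk, outcome 1 rises by 17 percentage points (340 / 2,000) and outcome 2 falls by 0.1 to 0.3 points. Meanwhile roughly a quarter to 30% of the low-risk group has a condition that is not low-risk. Calling all of them low-risk is the extreme case; a real tool would probably call only some of them so.

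This is a worthwhile, low-cost improvement to what is reported. It is not an error that invalidates the design, and the secondary outcomes already cover part of it.

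**What to change.** Keep the existing second primary outcome, the proportion high-risk among all patients the tool classes as low-risk. Beside it, at primary level, report the proportion with a high- or intermediate-risk condition in the same group, each with a 95% confidence interval. Base any statement about suitability for non-conveyance on both figures.

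The change takes about one sentence in the outcome definition and is best made before analysis. Discharge diagnoses and the three-class scheme are already planned, so no new data are needed. The downside is a headline error rate that is likely to be less favourable, since the added proportion can never be smaller than the high-risk proportion alone.
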